## Abstract

**Background:**

The preschool years are a critical window for obesity prevention efforts; representing a time when children establish healthy eating habits and physical activity patterns. Understanding the context in which these behaviors develop is critical to formulating a model to address childhood obesity. The Colorado LEAP Study, an intervention study designed to prevent early childhood obesity, utilizes a social ecological approach to explore individual, family and environmental factors and their relationship to child weight status over a 3 year timeframe.

**Methods:**

The study is located in 5 rural Colorado preschool centers and elementary schools (2 treatment and 3 control). Treatment sites receive *The Food Friends®* nutrition (12 weeks) and physical activity (18 weeks) interventions during preschool. Observational measures assess 3 layers of the social ecological model including individual, family and organizational inputs. Children’s food preferences, food intake, gross motor skills, physical activity (pedometers/accelerometers), cognitive, physical and social self-competence and height/weight are collected. Parents provide information on feeding and activity practices, child’s diet, oral sensory characteristics, food neophobia, home food and activity environment, height/weight and physical activity (pedometers). School personnel complete a school environment and policy assessment. Measurements are conducted with 3 cohorts at 4 time points – baseline, post-intervention, 1- and 2-year follow-up.

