## Methods/design

### Study design

The Colorado LEAP project is a longitudinal cohort study utilizing a controlled quasi-experimental design in 5 rural Colorado communities. Two communities serve as intervention communities with the other 3 as matched controls. Intervention sites will receive *The Food Friends®* nutrition and physical activity programs in preschool and ‘booster’ programming in kindergarten and 1^st^ grade. Assessments will be administered 4 times - twice in preschool (Fall and Spring) and once in both kindergarten and 1^st^ grade (Spring) (Figure 1). Observational measures of children will be conducted at the school; parent/home measures will be sent home and returned to school via the child; and school personnel will complete school environment and policy assessments. This study was approved by the institutional review boards at Colorado State University and the University of Colorado Denver Anschutz Medical Campus.

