#### Preschool: The Food Friends ®

*The Food Friends: Fun with New Foods (FWNF)* classroom program is a 12-week intervention developed by Colorado State University [22-26]. The length of the program is critical and was established from literature reviews and our own project evaluation data, confirming that 8–12 experiences are necessary for a child to try and accept a new food [15]. Classroom implementation will include: a 15–20 min nutrition activity 1×/week and opportunities to try new foods 2×/week. Various tactics bring *The Food Friends* to life in a playful and exciting manner. Child-centered activities and supporting materials were developed for 8 food characters and 13 novel foods [22,26]. Eight *Food Friends* characters are central to program themes and materials.

*The Food Friends: Get Movin’ with Mighty Moves (MM)* Classroom Program is 18 weeks in length, and will be conducted 4 days a week for 15–20 min/day, for a total of 72 lessons led by the teacher [27]. Each week will focus on a skill from 1 of the 3 gross motor skill categories: stability (e.g., balance), locomotor (e.g., running and jumping), or ball skills (e.g., throwing and kicking). Early in each week, children will be introduced to a motor skill with movement concepts added as the week progresses. Later in the program, skill patterns, a combination of more than one motor skill, will be incorporated into activities. Creatively, graphics depicting each of *The Food Friends* characters participating in different physical activities are incorporated throughout program materials. They illustrate the different motor skills presented to children as *Mighty Moves*. Both programs will utilize a superhero theme (Super Taster and Mighty Mover) to engage in desired behaviors in a fun and creative manner [27,28].

Teacher training at intervention schools will be conducted for both programs prior to classroom implementation addressing program materials, concepts, and child feeding and activity topics. Feeding topics will include neophobia, eating characteristics of 3- to 5-year olds, role modeling, and how to encourage children to try new foods. Hands-on and participatory activities demonstrate to teachers various ways of teaching motor skills and the *Mighty Moves* activities.

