### Data analysis

Data will be analyzed using SPSS 21.0 Windows (IBM SPSS Statistics, Inc., Chicago, IL) program. Descriptive statistics (e.g., percentage, mean, standard error, etc.) will be obtained for demographic, anthropometric, and weight status variables. Additionally, shape-based statistics will be calculated to test assumptions for parametric procedures; data not meeting assumptions will either be transformed or appropriate non-parametric procedures will be utilized. The statistical evaluation associated with the research questions will employ either MANOVA or ANOVA procedures followed by planned comparison t-tests. For example, to answer Question 1 that states *Food Friends®* and *Mighty Moves*™ increase willingness to try new foods and develop motor performance, and that these gains will persist throughout a three year period, a 2x2 MANOVA mixed model design will be used to assess the final outcome measures at the end of the last year. The two factors, are Treatment Intensity (2 levels; experimental and control groups), a between group factor, and Time (2 levels; pre and post treatment), a within group factor. The multiple dependent measures to be explored include the nutrition measures of food preferences, willingness to try, and dietary consumption along with physical activity measures including for example, gross motor skills, pedometer steps and accelerometer outputs. To test the specific hypotheses for Question 1, each dependent variable will be explored using 2x4 ANOVA design (the same factors as above but the within factor, Time, consisting of 4 time periods) followed by orthogonal *a priori* t-tests. Covariates will also be added to the basic ANOVA design to explore effects of age, sex, ethnicity, and location. The significance level will be set at α = 0.05 for all analyses.

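### Three cohorts are declared, but the Question 1 model has no cohort term, so an unequal cohort mix between arms could bias the treatment-by-time contrast by a small amount

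*Protocol article*

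**What the plan says.** The Methods paragraph of the abstract says "Measurements are conducted with 3 cohorts at 4 time points". The readable body does not describe these cohorts: it gives no entry years, no sizes and no split by arm. The study design figure is not shown, so it may say more.

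The Study design section describes a "longitudinal cohort study utilizing a controlled quasi-experimental design in 5 rural Colorado communities", with two intervention communities and three matched controls. The Sample size estimation section plans one two-group comparison of 100 children per group, calls the groups convenience samples, and mentions no cohort stratum.

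For Question 1, the Data analysis section sets out a MANOVA on treatment group and time, the latter being "Time (2 levels; pre and post treatment), a within group factor". Each outcome is then analysed in a 2x4 ANOVA, described as having "the same factors as above but the within factor, Time, consisting of 4 time periods". On adjustment, the section says: "Covariates will also be added to the basic ANOVA design to explore effects of age, sex, ethnicity, and location". Cohort is neither a factor nor a covariate.

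**The concern.** The plan declares a design feature and then leaves it out of a model whose factors, levels and covariates it names. No listed covariate stands in for cohort. Location identifies the site, and age at a given assessment should be nearly the same in every cohort if each enters preschool at the same age.

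If the cohorts are successive intakes, they can differ in calendar year and in how practised the teachers are with the programme. Randomisation stratified by cohort would balance such differences between arms. Here the arms are whole communities and the children are convenience samples, so recruitment could run at different rates by year in the two arms. Slower or faster change in one cohort would then be credited partly to treatment, and a model with only treatment and time could not show it.

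**Working it through.** **1. The plan's own figures.** For BMI, an effect of 0.50 SD at 80% power and two-sided α = 0.05 needs 63.8 per group by the exact t-test, so 64, as stated. For attrition, 90 / (1 − 0.10) = 100 per group, as stated. The effect size behind the 90 per group for motor skills is not given. At 90% power and two-sided 0.05 it solves to 0.486 SD by the t-test, or 0.483 SD by the normal approximation. None of these figures depends on cohort, so this point overturns no stated number.

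**2. When cohort matters.** Let p_k and q_k be the shares of cohort k in the intervention and control arms, and c_k the mean change in cohort k apart from any treatment effect, in SDs of change.

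Bias in the difference in change = Σ (p_k − q_k) × c_k

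- If the cohorts differ only in level, c_k is the same for all k. Because Σ (p_k − q_k) = 0, the bias is zero.
- If the mix is the same in both arms, every p_k − q_k is zero and so is the bias.
- Bias therefore needs both unequal mix and cohort-specific change.

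**3. Size of the bias (all inputs assumed; the document gives none).** Take c = 0, r/2, r for the three cohorts, where r is the first-to-last difference in change. For mirror-image mixes the formula reduces to (difference in first-cohort share) × r, apart from sign.

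| Mix, one arm vs the other | r = 0.2 SD | r = 0.3 SD |
|---|---|---|
| 40/33/27 vs 27/33/40 | 0.13 × 0.2 = 0.026 | 0.13 × 0.3 = 0.039 |
| 50/30/20 vs 20/30/50 | 0.30 × 0.2 = 0.060 | 0.30 × 0.3 = 0.090 |

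Written out for the last cell, the weighted means are 0.30 × 0.15 + 0.20 × 0.30 = 0.105 and 0.30 × 0.15 + 0.50 × 0.30 = 0.195, a difference of 0.09 SD.

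Against the implied 0.486 SD, these biases are 5%, 8%, 12% and 19%, in the order 0.026, 0.039, 0.060, 0.090.

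**4. Effect on the nominal 5% test.** With 90 per group the standard error is √(2/90) = 0.149 SD. The rejection rate with no true effect is 1 − Φ(1.96 − b/0.149) + Φ(−1.96 − b/0.149). This gives about 5.3%, 5.8%, 6.9% and 9.3% for the same four biases.

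**5. Equal mix.** Cohort-specific changes of −d, 0, +d in thirds add 2d²/3 to the variance of change. Power of 90% falls to 89.8% at d = 0.1 (r = 0.2) and 89.6% at d = 0.15 (r = 0.3). Even at d = 0.5, a full 1 SD between first and last cohort, it is 85.1%.

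**The case against.** The strongest reply is that this is an omission in a condensed article. A full analysis plan could add an intake-year term, the model is introduced as an example, and the missing design figure may define the cohorts. Pooling is inferred from the single two-group comparison and is not stated. Nor does the document show that the cohort mix differs by arm or that the cohorts change at different rates. All of this is fair, and it keeps the point small. It does not remove it: the article goes beyond deferring the model, naming the factors, their levels and the covariates, and a structure that its own abstract declares is not among them.

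Two stronger readings are tempting, and the document supports neither.

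- A reader might infer that any difference between cohorts distorts the treatment effect. It does not: a constant difference in level cancels from treatment-by-time.
- A reader might infer that children in later intervention cohorts had already received the programme before baseline, because teacher training covers "eating characteristics of 3- to 5-year olds". That phrase only names a feeding topic in the training. It does not show that three-year-olds sat in intervention classrooms or that children attended for two years, and Participant recruitment refers to four-year-olds. The document gives no share of previously exposed children and lists no prior-attendance data. Cohort terms common to both arms would not remove such an effect in any case.

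**Conclusion.** The point holds as a modest gap in a stated model. Three cohorts are declared, the Question 1 model carries no cohort term, and the non-randomised allocation does not protect the comparison from unequal cohort mix. Over the assumed range the bias is about 0.03 to 0.09 SD. With equal mix, the loss is under half a percentage point of power over the same range of cohort differences, and about 5 points in the extreme case.

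This rests on three assumptions that the readable text does not settle: the cohorts are successive intakes, they are pooled, and both the mix and the rate of change differ between them. The document does not show that the trial is biased, and no stated sample size changes. The reason to act is that protection is nearly free.

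**What to change.** In the Data analysis section, add cohort (3 levels) and cohort-by-time as fixed terms to the 2x2 MANOVA and the 2x4 ANOVAs. Report treatment-by-time-by-cohort as a descriptive check, since the study is not sized to test it. One sentence should define the cohorts and give their planned split by arm.

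The cohort-by-time term removes the mix bias described above when the cohort trends are common to both arms; the three-way check shows whether that is plausible.

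The cost is 2 degrees of freedom for cohort plus 2 × (2 − 1) = 2 for cohort-by-time in the 2x2 model, or 2 × (4 − 1) = 6 in the 2x4 model, with about 180 children analysed. No further assessment of children is needed.

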**Discussion:**

The design of this study allows for longitudinal exploration of relationships among eating habits, physical activity patterns, and weight status within and across spheres of the social ecological model. These methods advance traditional study designs by allowing not only for interaction among spheres but predictively across time. Further, the recruitment strategy includes both boys and girls from ethnic minority populations in rural areas and will provide insights into obesity prevention effects on these at risk populations.

**Trial registration:**

ClinicalTrials.gov: NCT01937481.

## Background

Childhood obesity continues to be a major public health concern, with rates increasing over the last thirty years [1]. Currently, more than 26% of preschool-aged children are considered either overweight or obese. Children and families from low socioeconomic and minority backgrounds; particularly in rural areas that have limited access to food, activity & health-related services, are disproportionately affected [1,2]. Despite the high need, early childhood has not been a focus of obesity prevention efforts [3].

The preschool years present a critical window in which to begin obesity prevention efforts as they represent a time when young children establish healthy eating habits and physical activity patterns [4]. Unfortunately, young children are not meeting nutritional or physical activity guidelines [5,6]. Because early childhood is one of rapid development, it may afford the best opportunities for altering development in ways that can reduce obesity risk [3]. Food preferences are developed *in utero* and in early childhood and tend to persist throughout life [7,8]. Cross-sectional research has demonstrated that children who are more willing to try novel foods and who are less food neophobic have higher quality diets than those children who are more food neophobic [9].

The causal factors contributing to low activity levels among preschoolers are not well understood, however it is posited that there may be a relationship between the status of children’s motor skill performance and their levels of physical activity [10,11]. Several studies have reported that children with poorer motor skill performance were less active than children with better-developed motor skills [10-14]. Interventions aimed at altering developmental pathways, such as influencing food neophobia and gross motor proficiency, may impact dietary consumption and physical activity levels in later childhood and have long term impacts on the risk for obesity. The most informative designs regarding the development of behaviors associated with eating and activity outcomes necessitate a longitudinal design which samples a variety of behavioral antecedents and outcomes.

*The Food Friends* program is one such intervention that has addressed developmental behaviors in young children. Comprised of two components *– Fun with New Foods®* and *Get Movin’ with Mighty Moves®* - the program has successfully demonstrated increases in both children’s willingness to try new foods (food preference) and gross motor performance in preschool-aged children [15,16]. Further exploration is warranted to understand social and environmental influences on these behaviors.

Children’s eating and activity behaviors are influenced by factors that are individual to the child, but also by the environments, in which they live, learn and play. Ecological models provide a framework for addressing interactions across individual, social and environmental spheres of influence [17,18]. Predictive behaviors within these environments can influence child behaviors. While many predictive behaviors have been shown to influence dietary intake, physical activity, and weight status; food preference and motor performance merit further exploration. Understanding the context in which child behavioral patterns are developed is critical to developing a model to address childhood obesity. Skouteris [19] makes the argument that children’s development is a bidirectional transaction, with parents influencing children but also children impacting parents’ decisions and behaviors. Understanding environments, parent behaviors and children’s behaviors over time will provide an opportunity to begin to develop transactional models.

The Colorado Longitudinal Eating And Physical activity (LEAP) Study utilizes a social ecological approach to explore individual, family and environmental factors and their relationship to child weight status over a 3 year timeframe. Our primary research questions are as follows:

1. Are behavior changes (e.g. increased willingness to try new foods and improved gross motor skills) positively influenced by a preschool nutrition and activity program, *The Food Friends®*, sustained through early elementary school?

2. Do *The Food Friends®* programs have an impact on reducing the percentage of children considered overweight and/or obese over a 3 year timeframe?

3. Do food preference and gross motor performance directly affect child weight status or are they mediators to dietary intake and physical activity?

## Methods/design

### Study design

The Colorado LEAP project is a longitudinal cohort study utilizing a controlled quasi-experimental design in 5 rural Colorado communities. Two communities serve as intervention communities with the other 3 as matched controls. Intervention sites will receive *The Food Friends®* nutrition and physical activity programs in preschool and ‘booster’ programming in kindergarten and 1^st^ grade. Assessments will be administered 4 times - twice in preschool (Fall and Spring) and once in both kindergarten and 1^st^ grade (Spring) (Figure 1). Observational measures of children will be conducted at the school; parent/home measures will be sent home and returned to school via the child; and school personnel will complete school environment and policy assessments. This study was approved by the institutional review boards at Colorado State University and the University of Colorado Denver Anschutz Medical Campus.

**Figure 1 F1:**
[figure not shown]
Colorado Longitudinal Eating And Physical activity (LEAP) study design.

### Participant recruitment

Families will be recruited via an informational and consent packet sent home with their 4-year-old child and during Parent Information events to be held at the preschools. The packet will be available in Spanish and in English and both English- and Spanish- speaking staff will be present during recruitment events to be inclusive of all families whose children attend the preschool. Written consent will be obtained from parents or guardians prior to enrollment in the study. Children with identified developmental issues (e.g. cerebral palsy and downs syndrome) will be included in study activities but removed from data analysis.

### Sample size estimation

This study is powered on mean change differences in gross motor skills between intervention and control children. The statistical evaluation associated with the research questions will employ either Multivariate Analysis of Variance (MANOVA) or Analysis of Variance (ANOVA) procedures followed by planned comparison t-tests. As such, a power analysis based on the formulas and tables proposed by Cohen [20] shows that to evaluate motor performance in children using the results of ANOVAs on gross motor measures reported by Bellows et al. [16], a sample size of 90 per group could detect significant differences in motor performance between the two groups with 90% power. A power analysis for changes in BMI with an improvement of .5 standard deviation by the intervention group over the control group (ES = .50) and a power level set at .80 would need a sample size of 64 per group to show statistical significance at α = .05. Further, because differences in assessing changes in food exposure have been detected in samples as low as n = 12, the power for this study was based upon motor skills. Thus, with 90 children per group the power is high enough to detect changes in motor performance while also having a sensitive environment to pick up effects on the nutrition measures. Finally, to account for potential 10% attrition rate, as seen in our previous studies, we are planning a potential study size of 200 children; that is, 100 children in each of the two convenience samples.

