### Intervention

*The Food Friends®* is a research-based preschool program designed to address childhood obesity by establishing healthful eating and physical activity behaviors in preschool-aged children. The program consists of two components: *The Food Friends: Fun With New Foods®* focuses on helping children increasing children’s willingness to try new foods and *The Food Friends: Get Movin’ With Mighty Moves®* aims to enhance preschoolers’ gross motor skill development. The program utilizes constructs of the social cognitive theory, tenets of social marketing, and is embedded within Bronfenbrenner’s social ecological framework [21]. Two study schools will receive the intervention in preschool and elementary school (kindergarten and 1^st^ grade) while the three schools in the control condition will receive standard curriculum.

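### The stated 90% power for motor performance assumes independent children, but treatment is allocated to two versus three communities, so the five-site design does not deliver it

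*Protocol article*

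**What the plan says.** The Sample size estimation section of the Protocol article names its basis: "This study is powered on mean change differences in gross motor skills between intervention and control children". The motor effect is obtained "using the results of ANOVAs on gross motor measures" in a cited earlier study, but its size is not printed. With Cohen's formulas and tables, "a sample size of 90 per group could detect significant differences in motor performance between the two groups with 90% power".

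For BMI the section takes a half-SD advantage for the programme (ES 0.50) as its target and reports that "a power level set at .80 would need a sample size of 64 per group to show statistical significance at α = .05". It plans on the larger motor figure, describes the power with 90 per group as sufficient, and adds 10% for attrition to reach 100 per group and 200 in all. No ICC or design effect appears.

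The Study design section assigns two communities to intervention and three to matched control. The Intervention section agrees: "Two study schools will receive the intervention in preschool and elementary school", while the three control schools follow their standard curriculum. Lessons are given to classes by the teacher. The Data analysis section plans MANOVA or ANOVA and t-tests on children, with location only among covariates added for exploration.

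**The concern.** Children in one community share teachers, school, local environment and assessment occasions, so their outcomes are likely to be correlated. When whole communities are allocated, that correlation inflates the variance of the difference between arms, and the inflation grows with the number of children per site. A power figure from a formula for independent children is then too high for any valid test. With only two and three sites, between-site variance also has to be estimated from very little information.

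This power statement is the article's only justification for the study size. If it is wrong for the design, readers are told that the study can reliably detect effects of a size that it may well miss. If the child-level tests are used unadjusted, a difference between communities may be reported as a programme effect.

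**Working it through.** **Inputs from the article.** 90 per group, 90% power (motor); 64 per group, ES 0.50, 80% power, α = 0.05 (BMI); 10% attrition; 200 children; 2 versus 3 communities.

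**Inputs assumed.** Two-sided test; equal site sizes within an arm, so 90/2 = 45 and 90/3 = 30 children per site; ICC (ρ) from 0.01 to 0.10; total SD of 1.

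**Step 1: reproduce the plan's figures.**
- BMI, normal approximation: n = 2(1.960 + 0.842)²/0.50² = 62.8, so 63. The noncentral t gives 79.5% power at 63 and 80.1% at 64. The stated 64 is therefore the unclustered two-sided t-test answer.
- Attrition: 90/0.90 = 100 per group, 200 in total. The whole inflation goes to attrition and none is left for clustering.
- Motor: no effect size is printed, so the figure can only be solved backwards. Normal approximation: d = (1.960 + 1.282) × √(2/90) = 0.483. Noncentral t: d = 0.486. (A one-sided test would imply 0.438.)

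**Step 2: variance with clustering.** With n = 90 per arm,

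v = [1 + (45 − 1)ρ]/90 + [1 + (30 − 1)ρ]/90 = (2 + 73ρ)/90

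The effective number per arm is 2/v = 180/(2 + 73ρ). At ρ = 0.01, v = 2.73/90 = 0.0303, SE = 0.174 and effective n = 66.

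**Step 3: power.** Normal reference: Φ(d/√v − 1.960). Site-level reference: noncentral t on 5 − 2 = 3 df (critical value 3.182), noncentrality d/√v.

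| ICC (assumed) | SE | Effective n per arm | Motor, d = 0.486: normal / 3 df | BMI, d = 0.50, 90 per group: normal / 3 df |
|---|---|---|---|---|
| 0 | 0.149 | 90 | 90% / 60% | 92% / 62% |
| 0.01 | 0.174 | 66 | 80% / 48% | 82% / 50% |
| 0.02 | 0.196 | 52 | 70% / 40% | 72% / 42% |
| 0.05 | 0.251 | 32 | 49% / 28% | 51% / 29% |
| 0.10 | 0.321 | 19 | 33% / 19% | 34% / 20% |

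Example, motor at ρ = 0.02: 0.486/0.196 = 2.48; Φ(2.48 − 1.96) = Φ(0.52) = 70%.

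**Step 4: what the unadjusted child-level test does.** It uses SE = √(2/90) = 0.149 whatever the ICC. Under no effect it rejects when |Z| exceeds 1.960 × 0.149/√v:

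| ICC (assumed) | Effective cut-off | False-positive rate | Apparent power at d = 0.486 |
|---|---|---|---|
| 0.01 | 1.68 | 9% | 87% |
| 0.02 | 1.49 | 14% | 84% |
| 0.05 | 1.17 | 24% | 78% |

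**Step 5: can more children repair it?** As the number of children grows without limit, v tends to ρ(1/2 + 1/3). At ρ = 0.05, v = 0.0417 and motor power cannot exceed 66% (normal) or 38% (3 df). The number of communities is the limit.

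**The case against.** Several points on the other side are sound.

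- **The arithmetic is not wrong.** 64 and 100 per group both follow from the stated inputs. The fault is an unstated independence assumption that the design contradicts.
- **The ICC is not in the documents.** The study is powered on change, and controls are matched. Stable differences between sites cancel in change scores, so the relevant ICC may lie at the low end. The abstract mentions three cohorts, so a single ICC over all children at a site is a simplification. These points affect the size of the loss. Any positive ICC still puts the power of a valid test below the stated figure.
- **d = 0.486 is back-solved.** It is not a documented assumption, and every motor figure above inherits it.
- **BMI is less affected than the 64 suggests.** The plan has 90 per group, not 64. At ICC 0.01 with a normal reference, BMI power is 82%, above the stated 80%. It is lower at the larger ICCs and on 3 df.
- **The 3-df test is not the planned one.** That is so, but the planned child-level tests do not hold their 5% level under clustering, so their apparent power is no defence. Nor does exploring location as a covariate settle the matter, because each site belongs to one arm only.

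A reader might also infer that both figures rest on a short-term effect that will fade by 1st grade, since the earlier work concerned "gross motor performance in preschool-aged children" and the MANOVA for Question 1 "will be used to assess the final outcome measures at the end of the last year". The documents do not support this. They give neither the size nor the follow-up of the earlier motor effect, attach no time point to the BMI effect, and continue the programme with boosters in kindergarten and 1st grade to sustain the gains. Any particular rate of decay would be invented.

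**Conclusion.** The concern holds for clustering. The 90% motor figure describes two groups of independent children, not two communities compared with three. Given d of about 0.486 (back-solved, two-sided), equal site sizes and an assumed ICC of 0.01 to 0.10, motor power is about 80% down to 33% with a normal reference, and 48% down to 19% on 3 df. The direction does not depend on the ICC chosen; the size does.

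For BMI the conclusion is milder: the stated 80% survives at ICC 0.01 with a normal reference and is lost otherwise over the range examined.

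A reader might infer that the main danger is a null result taken as proof of no effect. That applies once the analysis accounts for site. Under the child-level tests as written, the larger hazard is a spurious positive.

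**What to change.** Rewrite the Sample size estimation paragraph, without enlarging the trial:

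1. Print the motor effect size and SD actually taken from the earlier study, and whether the test is one- or two-sided.
2. Say that 90% power holds only if children within a community are uncorrelated.
3. Add a short table of power, or of detectable effect, over ICC 0.01 to 0.10 for five sites, using a test that accounts for site. On the assumptions above, the effect detectable with 90% power on 3 df is about 0.87 SD at ICC 0.01, 0.98 at 0.02 and 1.26 at 0.05.
4. Replace the statement that power is sufficient with this qualified one.

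The cost is one rewritten paragraph and a less favourable stated power. No children, sites or assessments are added.
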